### Consent process

School pastoral care teams are the initial point of contact for entry into the trial. Prior to any assessments of eligibility, pastoral care staff, briefed and trained on the details of the trial, identify which young people in their school they deem to be potentially eligible using the trial eligibility criteria. Pastoral care staff approach, and invite, potentially eligible young people for a pre-screening meeting to discuss the project, and if the young person expresses an interest in participating in the trial, and is willing to ask their parents/carers for signed consent, the pastoral care teacher sends a standardised trial letter to their parents/carers with information about the trial and consenting procedures. This method of identifying young people who may benefit from counselling reflects a relatively commonplace procedure in pastoral care referral to counselling services in UK schools. At this stage, it is explained to parents/carers that not every young person who is put forward to take part in the trial is eligible, and that assessment procedures are not a judgement about the young person or their problems, but an assessment of trial eligibility. Once parents/carers ‘opt in’ informed consent is obtained pastoral care staff make an initial referral to the ETHOS research team, on the basis of likelihood that the young person they have identified will meet all eligibility criteria during the assessment meeting. Informed parent/carer consent is obtained either in writing, or via the telephone with a member of the pastoral care staff or an ETHOS researcher acting as a proxy to obtain consent in this way. Consent obtained by proxy is either audio-recorded, or witnessed by a third party.

On receiving parent/carer consent, the young person is then invited to an assessment meeting with an ETHOS assessor. Assessment meetings are held in a confidential and secure environment within the school. The assessor talks the young person through the aims and nature of the trial, and explains to them the assessment and intervention procedures using an Information Sheet for Young People developed for the trial, during which time the young person has the opportunity to ask any questions they have about their potential involvement. During this meeting, the assessor makes a judgement as to whether they believe that the young person is of sufficient maturity and understanding to consent to participate in the research study, using Competence to Consent Guidelines developed for the trial. This judgement is made prior to any other assessment of eligibility; and the young person’s written, informed consent is obtained prior to any study procedures being carried out, or outcome measures being administered. The young person’s written, informed consent is required in addition to their parent’s/carer’s.

### Assessment

Where consent has been obtained from both the young person and their parent/carer, each young person is assessed for their eligibility into the trial by an assessor. All assessors are provided with comprehensive training in the study and the purposes and principles of the assessments. The primary measure for determining suitability for the trial is the Strength and Difficulties Questionnaire (SDQ) [35]. The SDQ measures psychological difficulties along 25 attributes, divided equally between five sub-scales: emotional symptoms, conduct problems, hyperactivity/inattention, peer-relationship problems, and prosocial behaviour. Respondents are required to respond to each of the 25 attributes by reflecting on the last 6 months. For each sub-scale, the score ranges from 0 to 10, with higher scores indicating greater difficulties. Young people completing the SDQ at the assessment meeting for the current trial are required to score ≥ 5 on the emotional symptoms sub-scale (SDQ-ES). Risk assessment is carried out following a discussion with the young person, and using the YP-CORE item 4 (‘I’ve thought of hurting myself”) which has a score range of 0 to 4, with higher scores indicating greater psychological distress [34]. If a young person scores ≥ 1 (on YP-CORE item 4) the assessor asks, in a sensitive and gentle manner, whether they feel that they are at risk to themselves or others, and makes a professional judgement using guidelines for assessing and managing risk developed for the trial. It is explained to the young person that, as there is an equal chance of being allocated to PCAU for 6 to 9 months prior to counselling, it is important for the research and pastoral care teams to know whether they need more immediate attention. If the young person is assessed as being in immediate danger or at risk of serious harm, procedures for onward disclosure and referral are followed. Assessors review the remaining criteria for participating in the trial with the young person before confirming their eligibility. All young people are asked to complete a demographic questionnaire in the first part of the assessment meeting. Figure 1 presents a flow chart of the progress of participants through the trial.

**Fig. 1 Fig1:**
[figure not shown]
Study flow chart of referral, screening and allocation of participants to the ETHOS study

### Randomisation

Consenting young people are allocated to one of two groups, SBHC or PCAU, via remote access to the central randomisation procedure that is hosted by an in-house vb.net application with a Standard Query Language (SQL) server backend at the Clinical Trials Unit, Manchester Academic Health Science Centre, University of Manchester (MAHSC-CTU). This is restricted access and users other than the system owner do not have access to future allocations. Sequence generation is, therefore, concealed from both the assessor and young person, as well as from the rest of the core research team. The randomisation ratio is 1:1 using the method of permuted blocks within school strata with adjacent block sizes themselves varying randomly within pre-specified limits.

### Blinding

Allocation of each participant to SBHC or PCAU is recorded in a separate Assessment Log used only by the assessors. Blinding of participants, providers and assessors is not possible, so this trial employs a ‘tester blind’ design wherein testers are blind to the young person’s allocation for the duration of the trial. To help ensure the success of the blind, a different tester is employed at 6 weeks/mid-point, 12 weeks/endpoint and 24 weeks/follow-up for each participant. The success of the blind is assessed by asking testers to report whether the participant or member of the pastoral care staff have revealed what group the participant is allocated to, on the predesigned Case Report Form (CRF) developed for the trial. Participants and school staff are asked not to reveal the group to which participants have been assigned, as far as is possible.

It is necessary to unmask the allocation of participants to testers conducting the mid-point/6-week meeting to allow the administration of the Working Alliance Inventory Short Form (WAI-S) [42] in the SBHC group (see below, ‘Measures’). Therefore, three separate CRFs have been developed at the mid-point/6-week meeting to ensure that the remaining measures are administered under blind conditions: CRF 1 contains all measures for administration to both groups and is used in the first part of the meeting, CRFs 2 and 3 contain measures only applicable to the SBHC or PCAU group, respectively, and are used in the second part of the meeting. Once CRF 1 has been completed by the participant, the participant’s allocation is revealed to the tester who opens a sealed envelope containing information as to which group the participant is in, and which CRF (2 or 3) should, therefore, be administered. Only testers conducting the mid-point/6-week test have access to the contents of the envelope, which is destroyed following use. The only measures completed following the unmasking of the tester are those relevant to the participant’s specific allocation.

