### Sample size

Sample size was calculated to take into account clustering and participants lost to follow-up. Firstly, without either clustering or participants lost to follow-up, for 90% power to detect a standardised mean difference (SMD) of 0.5, 86 participants would be required per arm (172 in total). The effect size was determined by pooling findings on the primary outcome from four previous studies and making a conservative estimate [24, 31–33]. Intra-class correlation coefficient (ICC) for counsellors was estimated from prior data as 0.05 [24, 31–33]. On average, we estimated that nine young people could be seen per counsellor (4.5 on average per assessment phase); if there is 20% loss to follow-up, this leaves a mean of 7.2. The ICC and average number of young people together leads to a design effect of 1.31, which, when multiplied by the pre-cluster sample size, gives 1.31 × 86 = 113 (rounded up). Hence, after loss to follow-up has taken place, 113/7.2 = 16 (rounded up) practitioners are required per arm. Add 1 [57] to give 17 counsellors. To find the number before loss to follow-up, we calculated 17 × 9 = 153 participants required per arm and 153 × 2 = 306 in total.

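### Assessors who confirm eligibility, partly by judgement, also use the log of past allocations within small blocked school strata, so the next allocation can be guessed better than chance

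*Protocol article*

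**What the plan says.** All of the relevant text is in the Methods/design part of the protocol article.

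- **Randomisation.** Allocation comes from a central system reached remotely. Only the system owner can see allocations still to come, and from this the article infers that the sequence is hidden from the assessor. The ratio is 1:1, "using the method of permuted blocks within school strata with adjacent block sizes themselves varying randomly within pre-specified limits". The limits are not stated.
- **Blinding.** "Allocation of each participant to SBHC or PCAU is recorded in a separate Assessment Log used only by the assessors". The same section says that assessors cannot be blinded.
- **Consent process.** At the assessment meeting "the assessor makes a judgement as to whether they believe that the young person is of sufficient maturity and understanding" to take part. This comes before any other eligibility check.
- **Assessment.** If the pupil scores 1 or more on the YP-CORE self-harm item, the assessor asks about risk and "makes a professional judgement using guidelines for assessing and managing risk developed for the trial". The main entry measure is a self-reported SDQ emotional symptoms score of at least 5. Assessors then go through the other criteria and confirm eligibility.
- **Measures; Training of assessors and testers.** The baseline battery is completed in the second part of the same meeting, and the assessors' guidelines cover its administration.

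**The concern.** Hiding the stored list prevents anyone from reading the next allocation. It does not prevent anyone from working it out. In permuted blocks, an excess in one arm must be repaid before the block closes, so a person who knows the past allocations in a stratum has information about the next one. Here that record is used by the people who decide entry.

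The motive needs no misconduct. The Assessment section links the risk discussion to the prospect of a 6 to 9 month wait for counselling in the PCAU arm, and assessors have, or are studying for, a counselling or psychotherapy qualification. An assessor who expects PCAU next might judge a borderline pupil too much at risk to enter, and accept a similar pupil when SBHC seems due. The arms would then differ for reasons that arise before randomisation. Intention-to-treat analysis does not address that, and baseline adjustment corrects only for what was measured.

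**Working it through.** **1. Size of a stratum.** The Sample size section starts from 86 per arm (SMD 0.5, 90% power). A t-test calculation gives 85.03, rounded up to 86, assuming a two-sided 5% level, which that section does not state. The ICC "for counsellors was estimated from prior data as 0.05", and "if there is 20% loss to follow-up, this leaves a mean of 7.2".

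- Design effect: 1 + (7.2 − 1) × 0.05 = 1.31
- 1.31 × 86 = 112.7, rounded up to 113
- 113/7.2 = 15.7, rounded up to 16; plus 1 = 17 counsellors
- 17 × 9 = 153 per arm; 153 × 2 = 306

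The plan's total is reproduced. Study setting gives 18 schools, so the average stratum is 306/18 = 17. With 4.5 young people per counsellor per assessment phase, and assuming one counsellor per school, about 9 per school enter in each phase over both arms.

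**2. Guessing model.** For each block scheme, 5,000 school sequences were simulated, with the allowed block sizes equally likely. The guesser knows all earlier allocations in the school but not the realised block sizes. The rule is to guess the arm that is behind, or toss a coin if the arms are level. This rule does not require knowing the block limits. A Bayes-optimal guesser who does know them scores the same to within 0.3 percentage points.

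**3. Hand check.** With fixed blocks of 2 and 17 entries, there are 8 certain guesses and 9 coin tosses: (8 × 1 + 9 × 0.5)/17 = 12.5/17 = 73.5%, with 8/17 = 47.1% certain. The simulation gives the same values.

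**4. Results.** The block limits are assumptions. Certain and 75% or better refer to a guesser who knows the limits.

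| Block sizes | Correct, 17 per school | Certain | Predictable at 75% or better | Correct, 9 per school |
|---|---|---|---|---|
| 2/4 | 70.8% | 10.1% | 52.5% | 69.5% |
| 2/4/6 | 68.9% | 3.4% | 56.1% | 67.5% |
| 4/6 | 67.8% | 5.9% | 43.6% | 66.3% |
| 4/6/8 | 66.5% | 2.5% | 37.3% | 65.2% |
| 6/8/10 | 64.8% | 1.9% | 26.8% | 63.4% |
| fixed 2 | 73.5% | 47.1% | 47.1% | 72.2% |
| fixed 4 | 69.7% | 31.3% | 31.3% | 68.4% |
| fixed 6 | 66.5% | 20.6% | 27.6% | 64.2% |

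Varying the block size sharply reduces certainty (about 2% to 10%, against 21% to 47% for fixed blocks). It lowers the average guessing rate much less.

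**5. From guessing to imbalance.** Suppose entrants predicted for SBHC and for PCAU differ in mean baseline distress by d, and guesses are right with probability p. The expected difference between arms is then (2p − 1)d. At p = 0.648 this is 0.296d, and at p = 0.708 it is 0.416d. This is before baseline adjustment and supposes that selection could act at every entry. The documents give no basis for a value of d, so no bias in the treatment effect can be calculated.

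**The case against.** The strongest reply is that the Randomisation section describes sound practice: central, restricted access and randomly varying block sizes. A reader might infer that its concealment statement is false. It is not. It is true of the stored sequence, and the gap lies only in what past allocations reveal.

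Several further objections stand.

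- A reader might infer that assessors consult the log before an assessment. The article does not say so. It also does not say whether one assessor covers a school, or whether allocations are released singly or in batches. The log is mentioned in a section concerned with keeping testers blind.
- Eligibility is not decided by judgement alone. The SDQ score is self-reported, and age, school-assessed attendance and parental consent are not assessor judgements. Competence is judged before any measure is given, and both competence and risk follow trial guidelines.
- The schools themselves are not small: Study setting puts three of 18 below 700 pupils. It is the number randomised per school that is small.
- Pastoral staff choose referrals and may learn allocations informally, but they do not hold the log, so they are not in the same position as assessors.
- The planned analyses adjust for baseline scores, which reduces imbalance in measured distress.

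These points limit the size of the risk. They do not remove it, because the arrangement as written gives the allocation history to those who confirm entry, and nothing stated keeps it from them until eligibility is settled.

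**Conclusion.** The point holds as a moderate and avoidable risk of selective entry, acting through the judgements of competence and risk. Its size is a correct-guess rate of about 65% to 71% at 17 per school (63% to 70% at 9), against 50% without usable knowledge of earlier allocations. This rests on the assumed block limits, equal recruitment across schools, and a guesser with a complete and current record for the school.

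It would go too far to conclude that upcoming allocations are mostly known, that selection took place, or that the treatment estimate is biased by some stated amount. Few allocations would be certain, there is no evidence on conduct, and a guessing rate is not a bias in the effect.

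**What to change.** Send each allocation to the trials unit, or to a project manager who does no assessments, and have that person hold the log and inform the counsellor and the school. Assessors should not see a school's earlier allocations until the pupil's eligibility and baseline measures are completed and locked. The log must also stay out of reach of the testers and the principal statistician, whom the plan keeps blind.

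The cost is a small change in who communicates the allocation. The change does not stop school staff from learning past allocations, so the referral route stays partly open.

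Releasing a school's allocations only after all its assessments in a phase would narrow that route within the phase, but it should be optional. Outcomes are timed from the assessment meeting, and ten school weeks of counselling leave at most 12 − 10 = 2 weeks before the endpoint, less where holidays intervene. Delay would use up that margin for the pupils assessed first.

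As a check, and as the main remedy if recruitment (due to finish in February 2018) is too far advanced, report the block limits and who had access to the log. Also report whether baseline YP-CORE differs by the allocation predicted from earlier allocations in the same school. A null result would be reassuring only for distress as measured, and it would say nothing about pupils turned away.

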### Measures

Once eligibility has been established, the second part of the assessment meeting requires participants to complete a battery of measures. In addition, eligible participants attend research meetings at 6 (mid-point), 12 (endpoint) and 24 (follow-up) weeks following their assessment meeting. Pastoral care staff at each included school work with the core research team to schedule research meetings with participants, and follow-up with participants if they are absent (e.g. due to sickness or a school trip). Research meetings are scheduled to fit into the each school’s individual daily timetable. A summary of the assessments, per time point, are presented in Fig. 2 and described below.

**Fig. 2 Fig2:**
[figure not shown]
Standard Protocol Item: Recommendations for Interventional Trials (SPIRIT) diagram of assessments at pre-screening, baseline/assessment, first session, session by session, mid-point/6 weeks, endpoint/12 weeks and follow-up/24 weeks

#### Primary outcomes

##### Young Person’s Clinical Outcomes in Routine Evaluation (YP-CORE)

The primary outcome measure is the YP-CORE [34], a 10-item, self-report, 5-point Likert-type scale measuring psychological distress. Participants are asked to rate how they have been feeling over the last week (prior to completing the questionnaire) in relation to 10 items. Individual item scores range from 0 (‘not at all’) to 4 (‘most or all of the time’) with a total YP-CORE score ranging from 0 to 40. The YP-CORE was chosen because it is a clinically relevant measure to assess changes in psychological distress in the age group being studied in the current trial, and because it has demonstrated internal reliability (*α* = 0.80) and test-retest reliability across 1 week (*r* = 76, 95% CI 0.65 to 0.86) [34]. The YP-CORE is administered at assessment/baseline, mid-point/6 weeks, endpoint/12 weeks, and follow-up/24 weeks.

##### Client Service and Receipt Inventory (CSRI)

The primary measure for evaluating cost-effectiveness is the CSRI, tailored towards the trial population. The CSRI is a measure widely used to comprehensively record support and services received by research participants (e.g. [43–46]). In the current trial, the CSRI collects information on service utilisation, school support, and accommodation in a manner commensurate with estimating costs [47]. The CSRI is administered at assessment/baseline and follow-up/24 weeks.

#### Secondary outcomes

A range of secondary, self-report outcome measures is collected in both groups. At assessment/baseline, mid-point/6 weeks, endpoint/12 weeks, and follow-up/24 weeks the SDQ [35] is collected to measure psychological difficulties, the Revised Children’s Anxiety and Depression Scale–Short Version (RCADS-SV) [48] collects data on depression and anxiety, the Rosenberg Self-esteem Scale (RSES) [49] collects data on self-esteem, the Student Engagement Scale–Behavioral Engagement sub-scale (SES-BE) [50] collects data about behavioural engagement at school, the Warwick-Edinburgh Mental Well-being Scale (WEMWBS) [51] collects data about level of well-being, and the Goal Based Outcome Record Sheet (GBORS) [52] measures degree of attainment towards personal goals. In addition, at endpoint/12 weeks, the Experience of Service Questionnaire (CHI-ESQ) [53] is administered to measure satisfaction with treatment provision. At the start of each counselling session, participants in the SBHC group are asked to complete the Outcomes Rating Scale (ORS) which assesses areas of life functioning known to change as a result of a therapeutic intervention [39].

In addition, at assessment/baseline and the follow-up/24-week point, schools provide data for educational indicators for each participant in the trial. This will include attendance rate, exclusion rate, detentions and disciplinary proceedings over the previous 3 months as well as current grades.

#### Mediators/predictors

All participants complete a demographic questionnaire at assessment/baseline. Additionally, in order to evaluate whether changes in young people’s levels of psychological distress is mediated by the quality of the relationship that they have with a professional (either counsellors or pastoral care teachers), and/or the quality of the alliance that they experience with their counsellor (for those allocated to SBHC), at mid-point/6 weeks we administer mediating/process measures of ‘Rogerian’ conditions (using the Barrett-Lennard Relationship Inventory Student Form (BLRI OS-40 T-S), [54] in both groups; and the therapeutic alliance (using the WAI-S [42]) in the SBHC group.

Counsellors and supervisors complete demographic questionnaires developed for the study. A researcher completes a School Characteristics Form, developed for the study, with a member of the school’s pastoral care team. This is to obtain data on the size and type of school, pastoral care provision, and characteristics of the general school population.

In the SBHC group, in the first counselling session, the counsellor completes the Current View [55] to record the young person’s characteristics and their presenting issues.

Adherence to the SBHC model is also measured (see above).

#### Qualitative interviews

Qualitative interviews are conducted with a sub-sample of participants, school staff and parents/carers at endpoint/12 weeks. Interviews seek to explore the schools’ staff perceptions on the effect of SBHC on the wider school, parents’/carers’ perceptions of the effect of SBHC on their children, and participants’ experiences of SBHC. We aim to conduct interviews with 50 participants from the SBHC group, and 20 parents/carers. In addition, ten focus groups with school staff will be conducted. The sample for the qualitative analysis is purposively sampled, to include ten schools out of the 18 schools participating in the research. The sampling strategy aims to ensure a mixture of local-authority-maintained schools, and academy schools; as well as a mixture of schools that have been awarded ratings of ‘needing improvement’, ‘satisfactory’, ‘good’, or ‘outstanding’ by the UK Office for Standards in Education. The sampling strategy also aims to ensure that the sub-sample of participants, school staff and parents/carers are drawn from schools of different sizes (in terms of the total population of pupils); and a mixture of same-sex and mixed-sex schools.

Once a school has been selected, all participants in the most recent cohort are asked to take part in a qualitative interview. This includes participants who have chosen to not take up all ten sessions of SBHC offered. In these cases, participants are not interviewed until the end of the intervention period for their cohort. Interviews are between 45 min and 1 h, and are scheduled during the school day. Questions focus upon participants’ views and experiences of SBHC and include questions about how they felt about being offered SBHC, their views about the counsellor, and what was particularly helpful and unhelpful about SBHC.

Key pastoral care staff in selected schools will be interviewed. In some settings it is possible to organise focus groups with relevant pastoral staff, while in others it is more appropriate and practical to organise one-to-one interviews with the main ETHOS school contact. Interviews last for approximately 1 h and questions focus upon understanding any changes that school staff have observed in the participants in the SBHC group, as well as any school-level change.

In addition, we approach all parents of participants in the most recent SBHC cohort. Interviews are conducted over the telephone and last between 30 to 40 min and aim to understand the impact of SBHC on the young person from the parent/carer perspective.

A thematic analysis will be conducted using NVivo for all interview data [56]. This method of analysis is used to examine and explore patterns or themes in the data. The following phases of analysis will be followed: (1) researchers familiarise themselves with the data by reading transcripts of interviews; (2) a list of initial codes across all interviews is generated; (3) potential themes are searched for by collating codes; (4) researchers review the themes in relation to the coded extractions; and (5) themes are refined.

The analysis of participant interviews will be designed to evaluate and refine an a priori logic model which draws on previous evidence to propose a theoretical framework for how SBHC engenders change [31].

